#### Safety outcomes

Adverse events (AE) will be monitored and promptly reported in this study through a dedicated safety monitoring team and a comprehensive reporting system. The team will track and document all adverse events, ensuring timely response and participant safety. AEs are described as dizziness, nausea, headache, or bruising. The causality with acupuncture will be analyzed by the acupuncturists. The occurrence, duration, severity (symptoms and signs), and corresponding solution of the adverse events should be recorded in detail in eCRFs. To ensure the safety of EA during the ovarian stimulation phase, all acupuncturists will be trained to perform EA according to standard operating procedures (SOPs). This ensures standardization and minimizes risks, guaranteeing the safety of participants during the IVF process.

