**Figure 1 f1:**
[figure not shown]
Flow diagram. IVF, *in vitro* fertilization; EA, electro-acupuncture.

**Table 1 T1:** Schedule of recruitment, intervention, and measures.

Items	Enrolment	Intervention	Follow-up			
	Screening and baseline assessment	Controlled ovarian hyperstimulation	Oocyte retrieval	Embryo transfer	14 days after embryo transfer	28 days after embryo transfer
Enrolment						
Eligibility screen	×					
Informed consent	×					
Allocation	×					
Baseline data	×					
Randomization						
Randomization	×					
Allocation	×					
Interventions						
EA/ pEA treatment		×				
COH treatment		×				
Assessments						
Laboratory tests	×	×	×	×	×	×
Embryo quality				×		
Pregnancy tests					×	×
Pregnancy outcomes				×	×	×
Fetus information						
FertiQoL	×		×			
SAS	×		×			
SDS	×		×			
PSQI	×		×			
Blinding assessments			×			
Adverse events		×	×	×	×	×
Retention rate						×
Adherence to treatment						×

EA, electro-acupuncture; pEA, placebo electro-acupuncture; COH, controlled ovarian hyperstimulation; FertiQoL, fertile quality of life; SAS, self-rating anxiety scale; SDS, self-rating depression scale. PSQI, Pittsburgh Sleep Quality Index.

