### Intervention

Patients in the three groups will receive GnRH-a or GnRH-A protocol according to the previous study (21, 22). Egg retrieval, fertilization, and embryo transfer were determined by their fertility specialists. During the study period, the patients’ medications, including dose and types, should be recorded in detail.

Following the randomization, the patients who were randomized into the EA + IVF group and the pEA + IVF group will receive EA treatment during the ovarian stimulation phase at three times per week (every other day) until trigger day with a minimum five session. Each session will continue for 30 min. Licensed acupuncturists possessing a minimum of 1 to 3 years of clinical experience will undergo training in a standardized operating procedure. This training aims to impart a comprehensive understanding of the precise locations of acupoints and non-acupoints. Additionally, they will acquire proficiency in needle manipulation and the operation of electro-devices. Only acupuncturists who have completed this training will be authorized to perform acupuncture treatments.

The disposable needles (Hwato, Suzhou, Jiangsu, China) and the SDZ-V EA apparatus (Suzhou Medical Appliance) have the same appearance. The needle device used for blinding is comprised of a sticky plastic plate with a guide tube. The needles and blunt-tip needles will be administered through the guide tube and the hole of the plastic plate.

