#### Electro-acupuncture

The treatment protocol, guided by the TCM theory, is aimed to enhance ovarian response and endometrium receptivity and served as an adjunctive non-pharmacological therapy. The treatment will involve the alternation between two sets of acupuncture points. Set 1 will administer in the supine position, including GV20 (*Baihui*), CV12 (*Zhongwan*), ST25 (*Tianshu*), CV 6 (*Qihai*), CV4 (*Guanyuan*), GB26 (*Daimai*), KI12 (*Dahe*), EX-CA1 (*Zigong*), SP10 (*Xuehai*), ST36 (*Zusanli*), SP6 (*Sanyinjiao*), and LR3 (*Taichong*). Set 2 will administer in the prone position, including BL23 (*Shenshu*), BL32 (*Ciliao*), and KI3 (*Taixi*) (see details in **Table 2**, **Figure 2**). All of the acupoints will be located according to the “WHO Standard Acupuncture Point Locations in the Western Pacific Region” (23). Following needle insertion, small, equal manipulations of twirling, lifting, and thrusting will be performed on all needles to reach *De qi* (a composite of sensations including soreness, numbness, distention, heaviness, and other sensations) (18). Paired alligator clips from the EA apparatus will be attached transversely to the needle holders at bilateral ST25 and EX-CA1 and at bilateral ST36 and SP10 in the supine position, while needles at bilateral BL23 and BL32 were in the prone position. The EA stimulation will be with a dilatational wave of 2/100 Hz and a current intensity of 0.1 to 5 mA depending on the participant’s comfort level (preferably with skin around the acupoints shivering mildly without pain).

**Table 2 T2:** Location of acupoints and manipulation techniques used for the EA+IVF group.

Acupoints	Location	Manipulation
Set 1 acupoints		
GV 20 (*Baihui*)	5 cun directly above the midpoint of the front hairline	Transverse insertion to a depth of 0.5 cun^a^–0.8 cun
CV12 (*Zhongwan)*	4 cun to the navel, on the upper abdomen middle	Inserted vertically to a depth of 1.0 cun–1.5 cun
ST25 (*Tianshu)*	Bilateral, 2 cun lateral to the umbilicus	Inserted vertically to a depth of 1.0 cun–1.5 cun
GB26 (D*aimai)*	Bilateral, 1.8 cun below to *Zhangmen* (*Zhangmen*, below the free end of the 11th floating rib)	Inserted vertically to a depth of 1.0 cun–1.5 cun
CV 6 (*Qihai*)	1.5 cun below the umbilicus, on the anterior midline	Inserted vertically to a depth of 1.0 cun–2.0 cun
CV4 (*Guanyuan*)	3 cun below the umbilicus, on the anterior midline	Inserted vertically to a depth of 1.0 cun–2.0 cun

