PSQI	PSQI contains 19 items, and its measurement is determined by calculating the sum of the scores of each item	Baseline and on trigger day
Adverse events		
	Including nausea during the ovarian stimulation, hematoma around the site of needling, infection around the site of needling, dizziness after acupuncture, and other discomforts after acupuncture	After each treatment

a The rates of pregnancy outcomes are defined as the number of pregnancy outcome cycle per ovarian stimulation cycle.

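### Adverse events have inconsistent, mainly acupuncture-related definitions and time frames, and no IVF-cycle complication is named as a safety outcome to be compared alike in all three arms

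*Protocol article*

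**What the plan says.** The Abstract names safety, alongside effectiveness, as something the pilot explores. Four places then deal with adverse events (AEs).

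- **Safety outcomes.** The section makes a general commitment: "The team will track and document all adverse events, ensuring timely response and participant safety". The next sentence is narrower: "AEs are described as dizziness, nausea, headache, or bruising".
- **Table 4 (Outcome measurement).** The entry is an inclusive list that opens with nausea during stimulation and continues "hematoma around the site of needling, infection around the site of needling, dizziness after acupuncture, and other discomforts after acupuncture". Its time frame is "After each treatment".
- **Table 1.** The row "Adverse events" is marked at stimulation, oocyte retrieval, embryo transfer, and 14 and 28 days after transfer.
- **Statistical analysis.** AEs are to be compared with chi-squared or Fisher's exact tests.

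Two other statements matter. Under Intervention, sessions run "three times per week (every other day) until trigger day with a minimum five session", and the IVF control group has no sessions. Under Electro-acupuncture, the treatment "is aimed to enhance ovarian response and endometrium receptivity".

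**The concern.** A safety comparison across three arms needs one definition of an event, asked about in the same way and over the same period in each arm. Here the text and Table 4 give different lists, and Table 4 and Table 1 give different periods. Most of the Table 4 items are tied to needling or to having had acupuncture, so women in the control arm cannot have them.

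The events that would inform on safety of the IVF cycle itself are not named as safety outcomes anywhere in the article. These are ovarian hyperstimulation syndrome, cycle cancellation for over-response, retrieval complications and ectopic pregnancy. Over-response deserves particular attention, because a treatment intended to enhance ovarian response might in principle enhance it too much. Peak E2 and oocyte number are collected, but Outcome measurement presents them as measures of ovarian function and not of safety.

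At stake is whether the pilot can say anything comparable across arms about harm during the IVF cycle, and whether it gives the larger trial a workable safety definition.

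**Working it through.** **1. The two lists side by side**

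| Item | Safety outcomes text | Table 4 |
|---|---|---|
| Dizziness | yes | yes, after acupuncture |
| Nausea | yes | yes, during stimulation |
| Bruising or hematoma | bruising | hematoma at needling site |
| Headache | yes | not named |
| Infection | not named | at needling site |
| Open category | none | other discomforts, after acupuncture |
| IVF-cycle complications | not named | not named |

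The text reads as a closed list. Table 4 is open, but only towards acupuncture. Of its five items (nausea, hematoma, infection, dizziness, other discomforts), one, nausea during stimulation, can occur in the control arm as worded. The placebo needles do not penetrate the skin, so hematoma or infection at a needling site is hardly expected in the placebo arm either.

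**2. The two time frames**

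Table 1 marks AEs in five columns. Sessions take place only during stimulation, so a per-session time frame covers 1 of 5 columns in the two acupuncture arms and 0 of 5 in the control arm. Retrieval, transfer and both later visits fall outside it.

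**3. What the sample can show**

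The planned size reproduces: 30 / (1 − 0.20) = 37.5, rounded up to 38 per arm, and 3 × 38 = 114. (The Abstract and the limitations give 118 instead. That is a separate matter; 38 is used here.)

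With 0 events in n patients, the one-sided 95% upper limit is 1 − 0.05^(1/n):

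- n = 38: 1 − 0.05^(1/38) = 0.0758, or 7.6%.
- n = 30 (the size before the dropout allowance): 1 − 0.05^(1/30) = 0.0950, or 9.5%.

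The documents give no rate for over-response, so the rates below are assumptions, shown over a range. Expected events are 38p. The chance of at least one event is 1 − (1 − p)^38. Power is for detecting a doubling between two arms of 38 (normal approximation, two-sided 5%).

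| Assumed rate p | Expected events per arm | Chance of at least one | Power against 2p |
|---|---|---|---|
| 1% | 0.4 | 32% | 5% |
| 2% | 0.8 | 54% | 7% |
| 5% | 1.9 | 86% | 13% |
| 10% | 3.8 | 98% | 23% |

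At every rate shown, a test between arms would be close to uninformative. Reporting counts with intervals is the realistic aim.

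**The case against.** The strongest reply is that the protocol already commits to tracking every AE, with occurrence, duration and severity recorded in the electronic case report form, and that Table 1 keeps collection open to 28 days after transfer. Table 4 is worded inclusively, and headache after a session fits its open item. Nausea, dizziness and headache can occur in any arm, and infection is not plainly minor, so it would be wrong to call the lists minor needling symptoms only. Early miscarriage is compared as an outcome, so adverse pregnancy outcomes are not all ignored. The article also condenses a fuller protocol, and itemised complications may sit in the case report form or operating procedures, which are not shown.

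Most of this stands, and it rules out two tempting inferences. A reader might infer that over-response would go unrecorded, or that the trial could declare electro-acupuncture safe without counting it. The documents support neither: the general commitment and the Table 1 schedule both allow such an event to be recorded, and nothing says that the two lists are a coding dictionary. Nor does any section say that a higher E2 level or oocyte count will be reported as benefit, and the link from intended response to over-response is an inference.

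The inconsistency remains. The general commitment is followed at once by a narrower description, and Table 4 sets a time frame that does not match Table 1. These are conflicts in stated text, not details left to another document.

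**Conclusion.** The point holds as an inconsistency in definition and timing, together with a gap in prespecification. Followed as written, Table 4 yields an AE comparison built largely on acupuncture-tied events, with no session at which controls are asked. IVF-cycle events may be recorded, but they are not assured of being counted and compared alike across arms.

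The defect affects the safety aim and leaves the primary outcome untouched. It should be corrected, but it does not invalidate the trial, whose results are already declared exploratory. The 7.6% limit comes from the pilot's size and would apply under any AE definition, so it bounds what may be concluded and is not a consequence of this defect. It assumes 38 evaluable women per arm. The 1% to 10% rates are illustrative assumptions, and the conclusion does not depend on them.

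**What to change.** 1. Reconcile the Safety outcomes text, Table 4 and Table 1 into one definition: any untoward medical event from randomisation to the end of follow-up, collected in the same way and at the same visits in all three arms. State when follow-up ends, because Table 1 stops at 28 days after transfer while Secondary outcomes follows pregnancies at 12 weeks.
2. Report needling-related events separately, for the electro-acupuncture and placebo arms only.
3. Prespecify IVF-cycle events as descriptive safety outcomes in all three arms: ovarian hyperstimulation syndrome, cycle cancellation for over-response, retrieval complications and ectopic pregnancy. Give counts by arm with confidence intervals.
4. State that with 38 per arm even zero events leaves a one-sided 95% upper limit of 7.6%, so the pilot can describe safety but cannot show it.

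This changes recording and reporting only, not clinical management. The cost is a protocol and case-report-form revision, a longer AE form, and some events in the report that are background to IVF. Trial status says that recruitment is under way, so women already enrolled may need their IVF-cycle events taken from clinical records. That those records hold the events is an assumption to confirm at the centre.

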### Blinding

Owing to the characteristics of the acupuncture procedure, the acupuncturists involved will not be blinded. In the EA + IVF group and pEA + IVF group, the single-blind will be conducted. The atmosphere of treatment, the communication between the acupuncturists and the patients, and the superficial appearance of the acupuncture techniques were the same. The apparatuses of the two groups are the same and can work normally. The study participants, fertility specialists, nurses, and the analyst were blinded to group allocation. The acupuncturists were not blinded to group allocation. Study site research physicians who were blinded to group allocation enrolled women in the study and collected clinical outcome data. Blinding was maintained until the completion of the analysis.

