### Statistical analysis

Intention-to-treat (ITT) analysis encompassing all randomized patients will be conducted for all efficacy analyses. Additionally, a per-protocol (PP) analysis focusing on the primary outcome will be performed as a sensitive analysis, excluding patients who did not complete the acupuncture treatment. Missing outcome data will be complemented using multiple imputations with the package “Mice” from the R software (www.r-project.org).

Categorical variables will be reported by number and percentage, whereas continuous variables will be represented by mean and standard deviation (SD) (or median and interquartile range, IQR). The retention rate and treatment adherence will be reported in descriptive statistics.

For the primary outcome, CPR will be compared by the proportions of included patients with clinical pregnancy. To determine the independent factors, logistic regression will be used to identify baseline variables that are associated with outcomes. The retention rate and rates of biochemical pregnancy, ongoing pregnancy, blinding assessments, and adverse events will undergo statistical analysis using chi-squared tests or Fisher’s exact test. Other outcomes will be evaluated using one-way variance (ANOVA) models or Kruskal–Wallis analysis. The score of SAS, SDS, FertiQol, and PSQI, respectively, will be assessed at baseline and after treatment among groups on hCG trigger day. Statistical significance will be determined at *P <*0.05. Pairwise comparisons will be performed between the EA + IVF group and the pEA + IVF group and between the EA + IVF group and the IVF group in a *post hoc* analysis.

A predetermined subgroup analysis will be performed to determine whether the baseline characteristics (female age, ovarian stimulation protocol, etc.) affect the CPR to EA. The data was analyzed using SPSS version 27.0 (IBM, Armonk, NY, USA). As this is a pilot study, our results were considered exploratory.

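### Relatedness of adverse events is judged by the unblinded treating acupuncturists, and Tables 1 and 4 set different adverse-event schedules, so comparisons with the IVF control group are at risk of unequal ascertainment

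*Protocol article*

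**What the plan says.** **Who judges relatedness.** Safety outcomes: "The causality with acupuncture will be analyzed by the acupuncturists". Blinding: "The acupuncturists were not blinded to group allocation". The Blinding section also says that research physicians unaware of allocation collect the clinical outcome data.

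**When AEs are recorded.** Table 4 gives the time frame as "After each treatment". In Table 1 the row "Adverse events" is marked at ovarian stimulation, oocyte retrieval, embryo transfer, and 14 and 28 days after transfer, with no split by arm. Safety outcomes describes a dedicated monitoring team: "The team will track and document all adverse events, ensuring timely response and participant safety".

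**What counts as an AE.** Table 4: "Including nausea during the ovarian stimulation, hematoma around the site of needling, infection around the site of needling", followed by dizziness and other discomforts, both tied to acupuncture. Safety outcomes: "AEs are described as dizziness, nausea, headache, or bruising".

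**How AEs are analysed.** Statistical analysis: "blinding assessments, and adverse events will undergo statistical analysis using chi-squared tests", or Fisher's exact test, at a 0.05 level. The section on the IVF control group says that it has no EA during stimulation.

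**The concern.** There are two separate problems.

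First, the people who deliver EA or placebo decide whether their own treatment caused an event, and they know which it was. The Highlights section itself names treatment providers as a likely source of bias. Attribution could shift events between related and unrelated differently in EA and pEA.

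Second, the two tables define different collection rules, and the article does not say which one supplies the AE rate to be analysed. If treatment in Table 4 means an acupuncture session, control women have no matching occasion to report. Background complaints of stimulation, such as nausea or dizziness, would then be recorded more fully in the acupuncture arms and could look like harm from acupuncture.

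Safety is a stated aim, and the pilot is meant to support a definitive trial, so the AE figures are likely to be carried forward.

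**Working it through.** **1. The passages side by side**

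| Item | Table 1 | Table 4 | Safety outcomes |
|---|---|---|---|
| Timing | Five points, stimulation to 28 days after transfer | After treatment sessions | Not fixed |
| Arms | Not split | Sessions exist only in EA and pEA | Not restricted |
| Dizziness | Not listed | Only if after acupuncture | Unconditional |
| Headache | Not listed | Not named | Named |
| Needle-site infection | Not listed | Named | Not named |

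Dizziness in a control woman is thus an AE under Safety outcomes but does not meet Table 4's wording. Nausea during stimulation, Table 4's first item, can occur in any arm.

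**2. Number per group.** From Sample size: 30 per group with 20% dropout. 30 / (1 − 0.20) = 37.5, rounded up to 38; 3 × 38 = 114. This reproduces the figure in that section.

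**3. Effect of unequal capture on a three-group test.** The article states no AE rate or capture rate, so both are assumptions. Set-up: 38 per group, the same true AE risk in all arms, full capture in EA and pEA, and a varying share captured in controls; Pearson chi-squared on the 3 × 2 table, 2 df, level 0.05; 200,000 simulated trials per cell. False-positive rate:

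| True AE risk | 100% captured in controls | 75% | 50% | 25% | 0% |
|---|---|---|---|---|---|
| 10% | 4.5% | 5.7% | 9.8% | 18.6% | 36.3% |
| 20% | 4.9% | 8.0% | 20.0% | 48.8% | 96.0% |
| 30% | 5.1% | 10.8% | 33.2% | 75.1% | 100.0% |
| 40% | 5.0% | 14.1% | 48.5% | 90.6% | 100.0% |

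With equal capture the test holds its level. At 10% risk the expected count is 38 × 0.10 = 3.8 per arm, so Fisher's exact test might be chosen and the rates in that row would differ.

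**4. How session contacts accumulate.** If a background complaint is reported at a fraction p of contacts (assumed) and contacts are independent, the chance of at least one report over the five-session minimum is 1 − (1 − p)^5: 9.6% at p = 0.02, 14.1% at 0.03 and 22.6% at 0.05. Complaints that recur in the same women would lower these figures.

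**5. Where relatedness enters.** The planned test is on AE rates and is not restricted to related events. Step 3 therefore does not measure the unblinded causality judgement, for which the article offers no figure.

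**The case against.** The strongest reply is that the plan already provides for AEs in every arm. Table 1 schedules them at all visits after enrolment without distinguishing arms, and the safety team documents all events. Table 4 does not say that sessions are the only occasion, nor that treatment there means acupuncture. This stands. A reader might infer that controls must show zero AEs; the documents do not support that, and a contrast of 10–23% against 0% would require setting Table 1 aside.

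A reader might also infer that unblinded attribution biases the planned AE test. It does not as written, because the test is not limited to related events. Nor does session timing by itself bias EA versus pEA, since both have the same session schedule. The three-group form of the AE test is itself an inference: the same sentence covers blinding assessments, which apply only to EA and pEA. It remains the natural reading for a three-arm trial.

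Needle-site haematoma or infection cannot occur in controls. That is a true difference in exposure, not an ascertainment bias. The AE lists may be meant as examples, with fuller definitions in operating procedures. The results are declared exploratory, and no pilot success target depends on AEs.

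These points limit the size of the concern. They do not resolve which table governs the analysed rate, and the safety team's documentation role does not change who is assigned to judge relatedness.

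**Conclusion.** The point holds in limited form. Unblinded providers judge relatedness, which puts the reporting of related AEs, chiefly EA versus pEA, at risk of bias of unknown size. Separately, Tables 1 and 4 conflict on AE timing, and Table 4 and Safety outcomes differ on what counts. Bias in comparisons with the IVF control group is a risk that depends on which rule is followed, not an established fact. It is absent if Table 1 is applied alike in all arms. Under partial capture it could be material: at an assumed true risk of 20%, the false-positive rate is 8.0% to 48.8% for control capture of 75% down to 25%. The exploratory status lowers the severity, but both matters are worth correcting because the correction is cheap.

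**What to change.** - Reconcile Table 1, Table 4 and Safety outcomes to one AE definition and to the Table 1 schedule, collected in the same way in all three arms.
- Use only those AEs in any comparison that includes the IVF control group. Report session-level and needle-site events for EA versus pEA only.
- Have relatedness judged, without the allocation, by members of the existing safety monitoring team who neither deliver treatment nor collect clinical outcomes. The blinded research physicians are less suitable: placebo needles do not penetrate the skin, so the description of a needle-site event could reveal EA allocation to those who record the clinical outcomes.

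The cost is a little assessor time and changes to protocol and eCRF wording. Needle-site descriptions may still partly reveal allocation to the safety-team assessor. Recruitment has begun, so some women may have had AEs collected under the present wording; their number by arm should be reported. The eCRF already calls for occurrence, duration and severity, so blinded relatedness review of events already recorded remains possible.
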